### Follow-up

An ultrasound evaluation will be integrated into the study’s follow-up process. Participants enrolled in both study groups will undergo thorough ultrasound assessments after each menstrual cycle. This evaluation will continue until either the cysts dissipate or for a maximum duration of three months.

### Sample size

Formula using mean difference

$$n1=n2=2\frac{{\left(Z_{\alpha }+Z_{\beta }\right)}^{2}\sigma^{2}}{{\left(\delta \right)}^{2}}$$

$$Z_{\alpha }=1.96$$

α=Type I error at 5% at both sides two tailed

$$Z_{\beta }=1.28=\text{Power at 90\%}$$

Dydrogesterone vs combined oral contraceptive pills for functional ovarian cysts (δ) = 0.3

Considering 30% superiority = (0.3*30)/100 = 0.09

Standard deviation = 1

Minimum sample size N =

$n1=n2=2\frac{{\left(1.96+0.09\right)}^{2}{\left(\;1\right)}^{2}}{{\left(0.09\right)}^{2}}=42\;\text{per group}$

Considering 10% drop out = 4

Total sample size required = 42 + 4 = 46 per group. Reference study.
^
5
^

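### The 42 per group at 90% power does not follow from the protocol's own formula and inputs, and the mean-difference model behind it does not match the planned test of cyst regression

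*Protocol article*

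**What the plan says.** The Sample size section of the protocol article is headed "Formula using mean difference" and prints n = 2(Zα + Zβ)²σ²/δ² per group. Its inputs are:

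- Zα = 1.96, described as "α=Type I error at 5% at both sides two tailed".
- Zβ = 1.28, labelled as 90% power.
- A difference: "Dydrogesterone vs combined oral contraceptive pills for functional ovarian cysts (δ) = 0.3".
- A second, smaller difference: "Considering 30% superiority = (0.3*30)/100 = 0.09".
- "Standard deviation = 1".

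The substitution line then reads 2 × (1.96 + 0.09)² × 1² / 0.09², with the result given as 42 per group. Drop-out follows, and the section closes with "Total sample size required = 42 + 4 = 46 per group". The outcome variable to which the mean difference and SD refer is not named.

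Two other places bear on this. The Statistical analysis section compares cyst regression within three months by a Chi-square or Fisher's exact test, which is a comparison of proportions. The Methods paragraph of the Abstract attributes the 46 per group to a 95% confidence interval and an estimated prevalence, and mentions neither power nor a mean difference.

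**The concern.** The general formula and the substituted line disagree on sight. The bracket should hold the two normal quantiles, 1.96 and 1.28, but holds 1.96 and the difference 0.09, and the same 0.09 appears again in the denominator. The value 1.28, the only carrier of the 90% power, is never used. The difference is also given twice, first as 0.3 and then as 0.09, without saying which one the trial is meant to detect.

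This calculation is the only worked justification for the size of the trial. If 42 does not come from it, the protocol has not shown what difference the trial can detect or with what power, and a reader who relies on the 90% figure is misinformed. It also matters that the calculation is on a different scale from the cyst-regression test: correcting the arithmetic alone would still not give the power of that comparison.

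**Working it through.** **Inputs**, all from the Sample size section: Zα = 1.96, Zβ = 1.28, σ = 1, δ = 0.3 or 0.09, stated n = 42 per group.

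**1. The plan's own line.** 2 × (1.96 + 0.09)² / 0.09² = 2 × 4.2025 / 0.0081 = 1,037.7. The stated result is 42, so it is not reproduced.

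**2. The stated formula with 1.28 in its place.** (1.96 + 1.28)² = 10.4976, so the numerator is 2 × 10.4976 = 20.9952.

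- δ = 0.3: 20.9952 / 0.09 = 233.28, so 234 per group.
- δ = 0.09: 20.9952 / 0.0081 = 2,592 per group (2,595 with unrounded quantiles).

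**3. Variants, in case another convention was meant** (per group, SD 1):

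| Variant | δ = 0.3 | δ = 0.09 |
|---|---|---|
| One-sided 5%, 90% power | 191 | 2,115 |
| Two-sided 5%, 80% power | 175 | 1,938 |

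At two-sided 5% and 90% power, δ = 0.3 + 0.09 = 0.39 gives 139 and δ = 0.3 − 0.09 = 0.21 gives 477. None of these gives 42. The nearest match among the printed inputs is 1.96² × 1² / 0.3² = 3.8416 / 0.09 = 42.7. That has the form of a precision calculation for a single mean, with no power term and no second group. The protocol does not say it was used, and it would not support a power claim.

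**4. What 42 per group delivers on the stated model.**

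- Difference detectable with 90% power: √(20.9952 / 42) = 0.707 SD. That is about 2.4 times 0.3 and about 8 times 0.09.
- Power is Φ(δ√(n/2) − 1.96) + Φ(−δ√(n/2) − 1.96), with √(42/2) = 4.583.
- δ = 0.3: 0.3 × 4.583 = 1.375, power 28.0% (noncentral t 27.4%).
- δ = 0.09: 0.09 × 4.583 = 0.412, power 7.0% (noncentral t 6.9%).
- If all 46 per group are analysed, these become about 30% and 7%.

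**5. The planned cyst-regression comparison.** The protocol gives no regression proportions, so the rates here are assumptions for illustration. The formula is the usual two-proportion one, two-sided 5%: n = [1.96√(2p̄(1 − p̄)) + 1.28√(p₁(1 − p₁) + p₂(1 − p₂))]² / (p₁ − p₂)², where p̄ is the mean of the two rates.

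For 10% vs 40%: [1.96 × 0.6124 + 1.28 × 0.5745]² / 0.09 = (1.9356)² / 0.09 = 41.6, so 42 per group. By symmetry 60% vs 90% gives the same.

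| Assumed rates | Power at 42 per group |
|---|---|
| 10% vs 40%, or 60% vs 90% | about 90% |
| 20% vs 50%, or 50% vs 80% | about 83% |
| 35% vs 65% | about 80% |
| Difference 0.30, lower rate 5% to 70% | about 80% to 98% |
| Difference 0.09, lower rate 5% to 70% | about 13% to 29% |

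Outside that range, 90% vs 99% gives about 44%. These figures carry no continuity correction. With one, 10% vs 40% needs 49 per group for 90% power instead of 42.

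**The case against.** The strongest reply is that the 0.3 may really be a difference in regression proportions. Cyst regression is analysed as a proportion, and a 0.30 difference between 10% and 40%, or between 60% and 90%, does need 42 per group at 90% power. On that view the number could be sound and only its derivation misreported.

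Part of this stands. The power of the cyst-regression comparison cannot be worked out from the document, so a reader who inferred that the trial simply has 7% to 28% power would go too far: that range belongs to the printed mean-difference model with SD 1. But the reply does not rescue the calculation. The section says it uses a mean difference, gives an SD, states no proportions, and reduces 0.3 to 0.09 before substituting. A 0.09 difference in proportions is poorly powered too.

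Two further inferences are tempting and should not be drawn.

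- That the drop-out step is a second error. "Considering 10% drop out = 4" adds a tenth of 42, while dividing by 0.9 gives 46.7, so 47. This is a one-patient difference of convention, and 46 × 0.9 = 41.4 still leaves about 41 to 42 evaluable.
- That the investigators will read a null result as showing that the drugs perform alike. The protocol makes no equivalence or non-inferiority claim, speaks of superiority, and plans two-tailed tests with confidence intervals where relevant.

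**Conclusion.** The point holds in this form: the sample size of 42 per group at 90% power follows neither from the stated formula, which gives 234 or 2,592 per group, nor from the line as printed, which gives about 1,038. On the stated model, with two-sided 5% and 42 evaluable per group, power is about 28% for 0.3 and about 7% for 0.09, and reaches 90% only at about 0.71 SD. The 90% claim is therefore unsupported.

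The model itself is the second half of the problem. It sizes a mean difference in an unnamed outcome, the analysis compares cyst regression as proportions, and the abstract cites a confidence interval and a prevalence. These three accounts must be reconciled. The arithmetic is certain. The power for cyst regression is unknown until proportions are stated, and under assumed rates it could be adequate for a 0.30 difference or low for 0.09.

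**What to change.** In the Sample size section:

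- Delete the substitution line and the 90% power claim.
- Name cyst regression as the endpoint being sized, and state the assumed regression proportion in each group with its source.
- Give one target difference, not both 0.3 and 0.09.
- State the power that 46 enrolled per group (about 41 to 42 evaluable) delivers for the Chi-square comparison at those proportions, and say whether a continuity correction or exact test was allowed for.
- If the mean-difference model is kept for a continuous outcome, name that outcome and say that 42 per group gives 90% power only for about 0.71 SD, with about 28% for 0.3 SD and about 7% for 0.09 SD.

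In the Abstract, change the stated basis of the sample size to agree.

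The cost is a rewritten paragraph, one sentence in the abstract, and a power statement that is less favourable or explicitly conditional. The fix itself requires no extra patients. The Study status section says the study has not started, so the correction can be made before recruitment.

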### Statistical analysis

The statistical analysis plan for this study will involve several key steps. Descriptive statistics will be used to summarize baseline characteristics of participants in both treatment groups. Continuous variables will be presented as means with standard deviations or medians with interquartile ranges, while categorical variables will be summarized as frequencies and percentages.

For the primary outcomes, the effectiveness and safety of the two treatments will be assessed separately. The regression of cysts within the three-month timeframe will be compared between groups using appropriate statistical tests, such as the Chi-square test or Fisher’s exact test. Changes in the menstrual pattern will be analyzed using paired t-tests or non-parametric tests if assumptions are not met.

Safety outcomes, including the duration of treatment needed and the incidence of side effects, will be compared using appropriate statistical tests, depending on the distribution of data. The impact on liver function tests and the occurrence of serious complications will be analyzed using appropriate statistical methods, potentially logistic regression, or survival analysis for time-to-event outcomes.

A comparative analysis between the two treatment groups will be performed using appropriate statistical tests, such as t-tests, Mann-Whitney U tests, or chi-square tests, depending on the nature of the data. Adjustments for potential confounders, such as age, BMI, and baseline cyst characteristics, will be considered using regression models. The significance level for hypothesis testing will be set at 0.05, and all tests will be two-tailed. Confidence intervals will be calculated where relevant.

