**Methods:**

This randomized controlled trial will be conducted over two years at the Department of Obstetrics & Gynecology, AVBRH, Datta Meghe Institute of Medical Sciences. The study population consists of reproductive-age women seeking care at the outpatient unit of Obstetrics and Gynecology at AVBRH hospital. The sample size of 46 participants per group has been calculated based on a 95% confidence interval and the estimated prevalence of functional ovarian cysts. Group A will receive low-dose COC for three menstrual cycles. At the same time, Group B will be administered dydrogesterone (10 mg twice daily) for ten days during the luteal phase, repeated across three cycles.

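### The stated 90% power belongs to an unnamed difference in means, does not follow from its own inputs, and does not apply to the cyst-regression comparison

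*Protocol article*

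**What the plan says.** Three places in the protocol article bear on the size of the trial.

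- **Sample size.** The calculation is introduced as "Formula using mean difference". Its error rate is "α=Type I error at 5% at both sides two tailed", and Zβ is 1.28 for 90% power. The effect is given as "Dydrogesterone vs combined oral contraceptive pills for functional ovarian cysts (δ) = 0.3", then reduced: "Considering 30% superiority = (0.3*30)/100 = 0.09". The spread is "Standard deviation = 1". The result is 42 per group, raised to 46 for dropout. No outcome or unit is attached to δ or to the SD.
- **Statistical analysis.** "The regression of cysts within the three-month timeframe will be compared between groups using appropriate statistical tests, such as the Chi-square test"; Fisher's exact test is the other one named. Under Primary outcome measures, ultrasound is repeated after each cycle until the cyst has gone or three months have passed, which fits a yes/no result. Cyst regression heads a list of several primary outcomes.
- **Abstract, Methods.** The 46 per group "has been calculated based on a 95% confidence interval and the estimated prevalence of functional ovarian cysts". No prevalence and no precision are given there or elsewhere.

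The article gives no regression rate for either arm and no target difference in rates.

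**The concern.** A power figure means something only for a given outcome, test and effect. Here the calculation is for a difference in means, the tests named for cyst regression are for categories, and the abstract describes a basis that is not visibly a two-group comparison at all. The three accounts of one number cannot all be right.

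What is at stake is how the result will be read. If the chi-square test is not significant, a reader who trusts the 90% may conclude that the two treatments perform alike. Whether that is fair depends on the difference in regression rates the trial could have detected, which the article never states. Its own two values of δ, 0.3 and 0.09, lead to very different answers.

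**Working it through.** **1. Reproducing the 42.** Inputs from the Sample size section: Zα = 1.96, Zβ = 1.28, SD = 1, δ = 0.3 or 0.09. Formula: n per group = 2(Zα + Zβ)²SD²/δ².

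| Version | Calculation | n per group |
|---|---|---|
| Stated inputs, δ = 0.09 | 2 × 3.24² / 0.0081 | 2592 |
| Stated inputs, δ = 0.3 | 2 × 3.24² / 0.09 = 233.3 | 234 |
| Expression as printed (0.09 where Zβ belongs) | 2 × 2.05² / 0.0081 | 1038 |
| Stated in the article | – | 42 |

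The 42 is not reproduced. At 90% power it would need δ = √(2 × 3.24² / 42) = 0.71 SD, which the article does not state. With 42 per group and SD 1, power is Φ(δ/√(2/42) − 1.96): about 28% for δ = 0.3 and about 6% for δ = 0.09.

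**2. Carrying the formula over to a proportion.** A yes/no outcome has an SD of at most 0.5, so SD 1 cannot belong to cyst regression. Putting in SD 0.5 gives 2 × 3.24² × 0.25 / 0.09 = 58.3, so 59 per group, for δ = 0.3, and 648 for δ = 0.09. These are upper bounds, because 0.5 is the largest possible SD. A two-proportions calculation at 90% power for a 30-point difference needs 28 to 57 per group, depending on the rates (34 to 63 with continuity correction).

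**3. What 42 evaluable per group deliver for cyst regression.** The rates p1 and p2 are assumptions, since the article gives none. Chi-square power, two-sided 5%, with d = p2 − p1 and p̄ their mean:

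Φ{[d − 1.96√(2p̄(1−p̄)/42)] / √([p1(1−p1) + p2(1−p2)]/42)}

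- 60% vs 90%: (0.30 − 1.96 × 0.0945) / 0.0886 = 1.295, so 90%.
- 40% vs 49%: (0.09 − 1.96 × 0.1084) / 0.1080 = −1.135, so 13%.

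| Difference | Lower rate (assumed) | Chi-square power | Fisher's exact power |
|---|---|---|---|
| 30 points | 40% | 80% | 76% |
| 30 points | 50% | 83% | 78% |
| 30 points | 60% | 90% | 87% |
| 30 points | 10% to 70% | 80% to 98% | – |
| 9 points | 40% to 60% | about 13% | about 10% |
| 9 points | 10% to 80% | about 13% to 21% | – |

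From a lower rate of 60%, 80% chi-square power is reached at 86.7% in the other arm; Fisher's test then has about 75%.

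**4. Precision.** The half-width of the 95% CI for the risk difference is 1.96√([p1(1−p1) + p2(1−p2)]/42).

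- 60% vs 90%: 1.96 × √(0.33/42) = 0.174, about ±17 points.
- 60% vs 86.7%: 1.96 × √(0.355/42) = 0.180, about ±18 points.
- Both arms at 50% or both at 60%: 0.214 or 0.210, about ±21 points.

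**5. The abstract's basis.** The usual calculation from a prevalence is 1.96²p(1−p)/(precision)². With assumed prevalences of 3% to 30% and precision of 5 or 10 points it gives 11 to 323. It contains no term for a difference between groups, so it carries no power for one.

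**The case against.** The strongest reply has four parts.

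*Cyst regression is only one of several primary outcomes.* Some others could be continuous, such as menstrual duration, treatment duration or liver enzymes, and t-tests are also mentioned. This stands as a limit on the claim: the article does not show that a sole binary primary endpoint was mis-sized. But δ and SD are not tied to any of those outcomes either, and step 1 shows that the 90% fails for any mean with the stated inputs.

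*The tests are given only as examples.* True, but both examples named for cyst regression are categorical, and no continuous measure of cyst size is defined as an outcome.

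*Details may sit in an analysis plan that is not shown.* That would answer an omission. Here a calculation is stated, does not reproduce, and conflicts with the abstract; a later document cannot make those statements agree. It is fair, though, that the abstract shows no formula, so reading it as a one-group precision calculation is an inference from its wording.

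*46 per group may well be enough.* This also stands. A reader might infer from the mismatch, or from the figures of 59, 234 or 2592, that the trial is too small. The documents do not support that: 59 is an upper bound, 234 and 2592 belong to a means comparison not planned for cyst regression, and if 0.3 was meant as 30 percentage points, 42 per group are roughly adequate. Whether such a difference is a reasonable target cannot be judged, because the article specifies none.

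**Conclusion.** The sample size statement is wrong as written. The 90% power cannot be claimed for the cyst-regression comparison, because it was derived for a difference in means with an SD no proportion can have. Nor can it be claimed for means, because the stated inputs lead to 234 or 2592 per group. The abstract adds a basis that does not match the body.

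No single power follows from the article's inputs. Depending on which of its two δ values is read as a difference in rates, chi-square power at 42 per group is either about 80–98% or about 13–21%. Those ranges rest on assumed regression rates (lower rate 10–70% and 10–80% respectively), two-sided 5% and 42 evaluable women per group; Fisher's test is a few points lower where it was calculated.

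The conclusion is limited to the justification: the power is misstated and the detectable difference undisclosed. It is not that the trial is underpowered.

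**What to change.** Withdraw the means-based calculation and its 90% claim. Keep 46 per group and state what that size delivers for cyst resolution by three months, as a two-proportions statement that names the test and labels the rates as assumptions. For example:

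> *No regression rates are assumed known. For illustration, 42 evaluable women per group give about 90% power by chi-square (87% by Fisher's exact test) for 60% vs 90%, and about 80% (75%) for 60% vs 86.7%, two-sided 5%. The 95% CI half-width for the risk difference is about ±17 to ±18 percentage points at those rates and about ±21 points if both arms are near 50–60%.*

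If the sponsor can support particular rates from the reference study, which is not available here, those should replace the illustrative ones. Such a statement describes what a fixed size can do; it should not be presented as the derivation of 46.

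Correct the abstract so that it gives the same basis, and report the risk difference with its 95% CI alongside the test.

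The cost is wording in the Sample size section, the Statistical analysis section and the abstract, plus a stated power that is less favourable and conditional. Keeping 46 adds no participants. The article says the study has not started, so the change can be made before any data exist.

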### Objectives

1.To study the effectiveness and safety of combined oral contraceptive pills in treating functional ovarian cysts.2.To study the effectiveness and safety of dydrogesterone in treating functional ovarian cysts.3.To compare the effectiveness and safety between combined oral contraceptive pills and dydrogesterone.

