### Primary outcome measures

**Effectiveness assessment:**
1.
**Regression of cysts:** To monitor the regression of ovarian cysts, we will conduct regular ultrasound evaluations. Participants from both study groups will undergo ultrasound assessments after each menstrual cycle. These assessments will continue until either the cysts dissipate or for a maximum duration of three months.2.
**Menstrual pattern changes:** To observe shifts in menstrual patterns, we will have participants maintain menstrual diaries. Participants will record information regarding the frequency, regularity, duration, and volume of their menstrual cycles. Data will be collected at each follow-up appointment, allowing us to track any changes over time.

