**Primary outcome measures:** The primary outcomes, centered around effectiveness and safety, encompass the regression of cysts, alterations in menstrual patterns, treatment duration, side effects, and complications. These outcomes holistically capture the impact of the interventions on both the physical and overall well-being of participants. Monitoring cyst regression and menstrual pattern changes offers insights into the interventions’ therapeutic effects, while evaluating safety profiles contributes to a comprehensive understanding of potential risks.

**Implications and future directions:** The findings of this study have far-reaching implications for clinical practice. The data generated from the study will aid clinicians in making informed treatment decisions, balancing effectiveness and safety considerations. Furthermore, this research sets the stage for more targeted investigations into the mechanisms of action of COC and dydrogesterone, potentially uncovering novel insights into the pathophysiology of functional ovarian cysts.

**Limitations and considerations:** It’s important to acknowledge potential limitations, such as the limited follow-up duration and the exclusive focus on two treatment options. Future studies could explore the effects of alternative interventions and longer-term outcomes, providing a more comprehensive understanding of functional ovarian cyst management.

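### The only test named for menstrual pattern change, a primary outcome, is a within-woman paired test, and nothing says which analysis decides the drug comparison

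*Protocol article*

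**What the plan says.** The Discussion of the protocol article counts menstrual change among the primary outcomes: "The primary outcomes, centered around effectiveness and safety, encompass the regression of cysts, alterations in menstrual patterns, treatment duration, side effects, and complications". Under Primary outcome measures it stands beside cyst regression as an effectiveness outcome with four components: frequency, regularity, duration and volume. The source is a diary: "To observe shifts in menstrual patterns, we will have participants maintain menstrual diaries". On timing the article adds: "Data will be collected at each follow-up appointment, allowing us to track any changes over time".

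The Statistical analysis section gives cyst regression a between-arm test: "The regression of cysts within the three-month timeframe will be compared between groups using appropriate statistical tests". The next sentence covers the menstrual outcome: "Changes in the menstrual pattern will be analyzed using paired t-tests or non-parametric tests if assumptions are not met". Two paragraphs later a general sentence follows: "A comparative analysis between the two treatment groups will be performed using appropriate statistical tests, such as t-tests, Mann-Whitney U tests, or chi-square tests". It names no outcome. Regression adjustment is to be considered, and the covariates offered as examples are age, BMI and baseline cyst characteristics.

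The first two Objectives take each drug on its own, for instance "To study the effectiveness and safety of dydrogesterone in treating functional ovarian cysts". The third is comparative: "To compare the effectiveness and safety between combined oral contraceptive pills and dydrogesterone".

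**The concern.** The two arms contain different women, so the only natural pairing is a woman's later value with her own earlier one. A paired test therefore estimates the change within an arm. That change mixes any drug effect with the natural course of the cycle and regression to the mean. No untreated arm is described that could separate these, and only the randomised contrast between arms removes what they share.

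An analyst who follows the sentence written for this outcome would produce two within-arm p-values and no estimate of the difference between the drugs. Such results are easily misread: if one arm is significant and the other is not, the first drug looks better, although no test of that has been made. If both are significant, the drugs look alike, although the changes may differ in size. An analyst who follows the general sentence instead would produce a between-arm test. The article gives no rule for choosing between the two on a primary outcome.

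**Working it through.** **1. What each sentence can answer.**

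| Statement in Statistical analysis | Comparison made | Menstrual outcome named? | Objective served |
|---|---|---|---|
| Cyst regression | Between arms | No | 3 |
| Menstrual pattern | Within woman (paired) | Yes | 1 and 2, descriptively |
| General comparative sentence | Between arms, unpaired | No | 3, if it is meant to apply |

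Only the second row names the outcome, and it does not make the comparison in objective 3. The third row could make it but is not tied to the outcome.

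**2. Size of the error if paired tests were used to rank the drugs.** The article gives no figure for the menstrual outcome, so there is none to reproduce. The two-sided 0.05 level comes from Statistical analysis. Let w be the probability that each arm's paired test is significant, with the same true change in both arms and independent arms. Then

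P(exactly one arm significant) = 2w(1−w).

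- No change in either arm, w = 0.05: 2 × 0.05 × 0.95 = 0.095.
- w = 0.5 (assumed): 2 × 0.5 × 0.5 = 0.50, the maximum.
- w = 0.8 (assumed): 2 × 0.8 × 0.2 = 0.32.

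**3. The same quantity by size of the common change.** Take n = 42 per arm (the Sample size section's figure before dropout, used here only as a number of evaluable women). Assume that the within-woman change has SD 1 and use the normal approximation. For a true change of θ SD,

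w = 1 − Φ(1.96 − θ√n) + Φ(−1.96 − θ√n).

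| θ (SD of change) | w | P(exactly one arm significant) |
|---|---|---|
| 0 | 0.050 | 0.095 |
| 0.1 | 0.099 | 0.179 |
| 0.2 | 0.254 | 0.379 |
| 0.3 | 0.494 | 0.500 |
| 0.4 | 0.736 | 0.388 |
| 0.5 | 0.900 | 0.180 |

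With 46 per arm the corresponding values are 0.095, 0.187, 0.397, 0.498, 0.350 and 0.141. A direct two-sample test of the changes rejects in 5% of trials in every row, because the true difference between arms is zero throughout.

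**The case against.** The best defence is that the article already plans a between-arm comparison. The general sentence excludes no outcome, and its three example tests suit continuous, ordinal and categorical items. Paired tests would then serve objectives 1 and 2, and the general sentence objective 3. This largely stands. A reader might infer that the menstrual outcome will never be compared between the drugs, and the text does not support that. What remains is that the specific sentence and the general one differ and that neither is named as decisive.

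Three further inferences also go too far:

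- **No pre-treatment diary exists.** The article says diary data are collected at follow-up appointments. It does not say that nothing is recorded at enrolment. A test of change presupposes an earlier value, and a condensed article may leave it to the full protocol. This is a point to confirm.
- **A t-test is forced on regularity.** No scale is given for regularity, and the sentence allows non-parametric tests.
- **The lack of baseline adjustment makes the analysis invalid.** In a randomised trial an unadjusted comparison of changes or of final values is valid. Adjustment usually gains precision.

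The defence is also right that the article nowhere says it will rank the drugs by which arm reaches significance. The percentages describe that hypothetical practice.

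**Conclusion.** The point holds in a limited form. The one test tied to this primary outcome cannot compare the two drugs, the general sentence that could do so does not mention the outcome, and the article does not say which decides. That is a badly fixed choice of analysis. It is neither proof that a comparison is absent nor a flaw in the cyst-regression analysis, which is explicitly between arms.

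The size is conditional. If separate paired tests were used to rank the drugs, equal true changes would give a split result in 9.5% of trials with no change, rising to at most 50%, against 5% for a direct test. This assumes independent arms and equal true changes. The values w = 0.5 and w = 0.8, and the SD of 1 for the change, are assumptions that no figure for menstrual change in the article supports. These percentages should not be read as error rates of the plan as written. Severity: should-fix.

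**What to change.** Replace the menstrual sentence in Statistical analysis with a between-arm comparison of each component at a common time point, three months from start, adjusted for the baseline value of that component:

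- continuous items: ANCOVA, outcome = intercept + arm + baseline value;
- categorical items: logistic or ordinal regression with the same terms;
- report the arm effect with its 95% confidence interval;
- keep paired within-arm changes as description for objectives 1 and 2.

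The time point needs a matching data rule. Ultrasound assessments end when the cyst dissipates, and treatment duration is described as depending on individual response, so women may otherwise be observed for different lengths of time. State that all randomised women keep the diary to three months, whether or not the cyst has resolved. The Interventions section withdraws from the study women whose allocated treatment is discontinued or modified, so it should say whether their diary follow-up continues.

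Confirm that the same four items are recorded at enrolment for the pre-treatment cycle, and add them if they are not. Also say which component leads, or how the four are handled together: four independent tests at 0.05 would give 1 − 0.95⁴ = 18.5% for at least one false positive.

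The cost is a few sentences of plan text, diaries continued to three months and, if needed, four questions at enrolment. The article states that the study has not started, so the baseline items can still be collected prospectively.
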